APPENDIX 1: SCHEDULE OF INVESTIGATIONAL EVENTS [23](#__RefHeading___Toc45188561)

Abbreviations and definition of terms

| ACE | Angiotensin-Converting Enzyme |
| --- | --- |
| ACR | American College of Rheumatology |
| AE | Adverse Event |
| ALAT (ALT) | Alanine Transaminase (SGPT) |
| ALP | Alkaline phosphatase |
| ANA | Anti Nuclear Antibodies |
| ASAT (AST) | Aspartate Transaminase (SGOT) |
| AUC | Area Under the Curve |
| CNS | Central Nervous System |
| CRF | Case Report Form |
| CRP | C-Reactive Protein |
| ECG | Electrocardiogram |
| ESR | Erythrocyte Sedimentation Rate |
| GFR | Glomerular Filtration rate |
| GGT | Gamma Glutamyl Transferase |
| HIV | Human Immunodeficiency Virus |
| MMF | Mycophenolate Mofetil |
| mRSS | Modified Rodnan Skin Score |
| NYHA | New York Heart Association Functional Classification |
| PAH | Pulmonary Arterial Hypertension |
| PK  QoL  SF-36  SHAQ  SSc  STPR  WBC | Pharmacokinetic  Quality of Life  Short Form (36) Health Survey  Scleroderma Health Assessment Questionnaire  Systemic Sclerosis  Skin Thickness Progression Rate  White Blood Count |

# study OBJECTIVES AND STUDY ENDPOINTS

## Primary Objective

- To study changes in disease related biomarkers in patients with progressiveSSc during treatment with ABR-215757

## Secondary Objectives

- To assess the safety and tolerability of ABR-215757 in progressive SSc patients
- To assess disease activity and quality of life (QoL) in patients with progressive SSc during treatment with ABR-215757.
- To assess plasma levels of ABR-215757 during the study

## Primary Endpoint

• Changes in SSc disease activity related biomarkers

## Secondary Endpoints.

- Adverse events and changes in laboratory safety parameters.
- Disease activity
- Quality of life measured by the SF-36 health survey and by the scleroderma health assessment questionnaire (SHAQ)
- Plasma levels of ABR-215757

# INVESTIGATIONAL PLAN

## Overall Study Design

Patients with progressive SSc will be treated with ABR-215757 in an open label single arm study. Patients presenting with progressive SSc with skin lesions on one or both forearms and a baseline mRSS score of at least 16 may be included in the study.

After a screening period of 14 ± 7 days, patients will be treated with 3.0 mg ABR-215757 daily for 8 weeks as the only treatment that is added to ongoing SSc medication. The dose may be reduced to 1.5 mg/day depending on the tolerability of ABR-215757 in individual patients. During treatment, there will be scheduled visits on days 14, 28 and 56. A follow-up visit will take place 4 weeks after last dose of ABR-215757.

Primarily, the study will involve the assessment of disease related biomarkers during treatment, compared to baseline. Secondary objectives of the study will involve assessment of safety parameters and SSc disease activity.

At specified time points during the study, blood samples and biopsies will be collected for analysis of biomarkers. Such assessments will include markers of vasculopathy, immune activation and fibrosis. SSc disease activity indices, including mRSS, will be followed. Safety parameters and ABR-215757 plasma levels will be monitored throughout the study. Allowed concomitant SSc treatment will include proton pump inhibitors, prostacyclin analogues and ACE inhibitors. Oral calcium channel antagonists, phosphodiesterase inhibitors and prednisolone (or equivalent) at a dose of ≤10 mg/day will be allowed at stable doses from specified time points prior to the study and throughout the study.

Patents may at the investigator’s discretion be offered to continue treatment after the planned 8 weeks main study. Study medication for treatment continuation will be dispensed at visit 6 and patients will return to previous treatment. Patients in continuation phase will be followed up in terms of safety and disease activity (mRSS) after 28 ± 7 days and thereafter every 84 ± 14 days (12 weeks). Treatment may continue until the next scheduled visit after the last patient entering the main study has reached visit 5/EW.

## Overall study Plan

Schedule of Investigational Events (see appendix 1)

**Main study**

*Visit 1, Screening visit, Day -14 ± 7 days*

The following procedures/evaluations will be performed at this visit:

- Written Informed Consent Form – must be obtained before any study-related procedures are performed
- Assignment of screening number
- Demography
- Medical history
- Urine Pregnancy test (if applicable)
- Urine dipstick (urinalysis)
- Assignment of patient screening number
- Physical examination
- Height and weight
- Vital signs (pulse rate, blood pressure)
- 12 lead Electrocardiogram (ECG)
- Clinical Assessment – mRSS , Digital Ulcers
- Sampling for clinical chemistry, hematology and coagulation
- Blood Sampling (biomarkers)
- Adverse Event questioning
- Review concomitant medications(s)
- Eligibility Checklist

*Visit 2, Baseline visit, Day 0*

The following procedures/evaluations will be performed at this visit.:

- Quality of life questionnaires (to be completed by the patient)
- Urine Pregnancy test (if applicable)
- Urine dipstick (urinalysis)
- Weight
- Vital signs (pulse rate, blood pressure)
- 12 lead Electrocardiogram (ECG)
- Clinical Assessment – mRSS , Digital Ulcers
- Adverse Event Questioning
- Review of Concomitant Medications(s)
- Eligibility check
- Assignment of enrollment number
- Sampling for clinical chemistry, hematology and coagulation
- Blood sampling (biomarkers).
- Skin Biopsy
- Sampling for ABR-215757 concentration in plasma (Predose)
- Dispensing of study medication - The first dose of ABR-215757 should be taken at the clinic, after all baseline assessments have been performed

*Visit 3, Day 14 ± 3 days*

The following procedures/evaluations will be performed at this visit:

- Weight
- Vital signs (pulse rate, blood pressure)
- Adverse Event Questioning
- Review of Concomitant Medication
- Sampling for clinical chemistry, hematology and coagulation
- Blood sampling (Biomarkers)
- Sampling for ABR-215757 concentration in plasma (predose)
- The daily dose of ABR-215757 should be taken at the clinic, after all assessments have been performed.

*Visit 4, Day 28 ± 7 days*

The following procedures/evaluations will be performed at this visit:

- Urine Pregnancy test (if applicable)
- Urine Dipstick (urinalysis)
- Weight
- Vital signs (pulse rate, blood pressure)
- Clinical Assessment – mRSS, Digital Ulcers
- Adverse Event Questioning
- Review of Concomitant Medication(s)
- Sampling for clinical chemistry, hematology and coagulation
- Blood sampling (Biomarkers)
- Sampling for ABR-215757 concentration in plasma (predose)
- Retrieval of Unused Study Medication and Accountability of study Medication
- Review of Treatment Compliance
- Dispensing of study medication - The first dose of ABR-215757 should be taken at the clinic, after all other assessments have been performed

*Visit 5, Day 56 ± 7 days*

The following procedures/evaluations will be performed at this visit:

- Quality of life questionnaires (to be completed by the patient)
- Urine Pregnancy test (if applicable)
- Urine Dipstick (urinalysis)
- Weight
- Vital signs (pulse rate, blood pressure)
- Clinical Assessment – mRSS, Digital Ulcers
- Adverse Event Questioning
- Review of Concomitant Medication(s)
- Sampling for clinical chemistry, hematology and coagulation
- Blood sampling (Biomarkers)
- Biopsy
- Sampling for ABR-215757 concentration in plasma
- Retrieval of Unused Study Medication and Accountability of study Medication
- Review of Treatment Compliance

*Visit 6, Day 84 ± 7 days*

The following procedures/evaluations will be performed at this visit:

- Quality of life questionnaires (to be completed by the patient)
- Urine Pregnancy test (if applicable)
- Urine Dipstick (urinalysis)
- Weight
- Vital signs (pulse rate, blood pressure)
- Clinical Assessment – mRSS, Digital Ulcers
- Adverse Event Questioning
- Review of Concomitant Medication(s)
- Sampling for clinical chemistry, hematology and coagulation
- Blood sampling (Biomarkers)
- Sampling for ABR-215757 concentration in plasma

**Continuation (optional)**

*Visit 7, Day 112 ± 7 days*

The following procedures/evaluations will be performed at this visit:

- Clinical Assessment – mRSS
- Urine Pregnancy test (if applicable)
- Adverse Event Questioning
- Review of Concomitant Medication(s)
- Sampling for clinical chemistry (CRP, AST, ALT, ALP, GGT and bilirubin)
- Retrieval of Unused Study Medication and Accountability of study Medication
- Review of Treatment Compliance
- Dispensing of study medication

*Visit 8, 9..N, Day 196, 280..m (± 14 days)[[1]](#footnote-2)*

The following procedures/evaluations will be performed at this visit:

- Clinical Assessment – mRSS
- Urine Pregnancy test (if applicable)
- Adverse Event Questioning
- Review of Concomitant Medication(s)
- Sampling for clinical chemistry (CRP, AST, ALT, ALP, GGT and bilirubin)
- Retrieval of Unused Study Medication and Accountability of study Medication
- Review of Treatment Compliance
- Dispensing of study medication (no dispensing at visit N = end of treatment visit)

*Continuation telephone follow-up, 28 ± 7 days after the end of treatment visit*

The following procedures/evaluations will be performed at this visit:

- Adverse Event Questioning
- Review of Concomitant Medication(s)

## Discussion of Study Design

All patients will initially receive ABR-215757 at 3.0 mg/day. The dose may be reduced to 1.5 mg/day depending on the tolerability of ABR-215757 in individual patients. The selected dose level, 3.0 mg/day ABR-215757 is predicted to be effective based on preclinical studies of autoimmune disease. Previous experience in humans as well as in preclinical models supports safe administration of ABR-215757 at doses up to and including 3.0 mg/day. The duration of the study is expected to be sufficient to detect changes in disease related biomarkers in this group of patients. Near steady state plasma levels of ABR-215757 in humans are reached in 14 days.

# SELECTION OF STUDY POPULATION

## Screening procedure

All patients will provide voluntary, signed written informed consent and complete all screening procedures at visit 1. Patients that are screened, but not eligible for the study should be listed, and reason for not being eligible should be noted.

## Number of patients

Approximately15 patients. Maximum 20 patients may be included with the aim to achieve at least 10 completed patients.

## Inclusion Criteria

Signed Informed Consent must be obtained before any study specific procedures takes place.

To be eligible for study entry, a patient must satisfy all of the following criteria:

1. Age ≥ 18 years at the time of signing the informed consent form
2. Clinical diagnosis of SSc according to ACR criteria
3. Progressive SSc fulfilling at least one of the following:
   - Skin thickness progression rate (STPR) ≥ 40, calculated as the mRSS at screening divided by time (in years) since the start of skin involvement, as reported by the patient (Denton 2007).
   - Worsening of mRSS within the last 6 months or shorter as judged by the physician together with the patient, with involvement of at least two new anatomical sites as defined in the mRSS score (e.g. upper arm and thorax) or progression by at least two points in at least two anatomical sites as defined by the mRSS.
4. Presence of SSc skin lesions on one or both forearms
5. Modified Rodnan Skin score (mRSS) ≥16 at baseline
6. ANA-positive

## Exclusion Criteria

A patient will be excluded from participation in the study if one or more of the following statements are applicable:

1. Ongoing Severe SSc manifestations, such as pulmonary arterial hypertension (PAH) with dyspnea NYHA III or more, scleroderma renal crisis.
2. Vital capacity < 60% as measured within 6 months prior to the first dose of study medication
3. GFR < 30% of normal as measured within 6 months prior to the first dose of study medication
4. Treatment with Rituximab within 12 months or other biologic agent within 6 months, Mycophenolate mofetil (MMF) or Cyclophosphamide within 6 months, Methotrexate, Azathioprine or other immunosuppressants within 3 months prior to the first dose of study medication.
5. History of myocardial infarction or current uncontrolled angina, severe uncontrolled ventricular arrhythmias, symptomatic congestive heart failure, unstable angina pectoris, or electrocardiographic evidence of acute ischemia.
6. Marked baseline prolongation of QT/QTc interval (*eg* repeated demonstration of a QTc interval >450 milliseconds)
7. History of additional risk factors for torsade de pointes (*eg* heart failure, hypokalemia, family history of long QT syndrome)
8. Treatment with concomitant medications that prolong the QT interval.
9. History of, or current ischemic CNS disease.
10. Current malignancy. A 5-year cancer-free period is required with the exception of skin basal or squamous cell carcinoma or cervical cancer in situthat has been excised.
11. Current severe infection
12. Known positive serology for HIV or active or latent hepatitis infection.
13. Treatment with endothelin receptor antagonist within 6 weeks prior to the first dose of study medication
14. Drug abuse
15. Major surgery within 3 weeks prior to study entry.
16. Known or suspected hypersensitivity to ABR-215757 or excipients.
17. Female patient of child-bearing potential who is not using a medically accepted safe method of contraception. All female patients of child-bearing potential must have a negative urine pregnancy test at the Screening and Baseline Visits. As interaction studies between ABR-215757 and hormonal contraceptives have not yet been performed, women using the hormonal contraceptives such as the contraceptive pill, must also use a complementary contraceptive device, i.e. barrier method, during the treatment period and for at least 1 month thereafter.
18. Female patient of child-bearing potential who is pregnant or lactating.
19. Simultaneous participation or participation within 4 months or 5 half lives (whichever is longer) prior to study entry in any other study involving investigational drugs or other experimental therapy.
20. Other significant, unstable medical disease not related to SSc that in the investigator’s opinion would confound the study result or put the patient at risk.
21. Patients likely to receive oral or intravenous steroids or immunosuppressant for other non-SSc condition during the study duration, as this will confound the study result.
22. Vaccination within 4 weeks prior to the first dose of study medication.

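### Exclusions 2 and 3 accept lung and kidney values up to 6 months old in patients selected for recent progression, and neither test is scheduled at screening, so a later decline below the protocol's own limits may be missed in some patients

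*Protocol*

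**What the plan says.** Section 3.4 of the protocol sets two numerical organ limits, both judged on a past result. Exclusion 2 is "Vital capacity < 60% as measured within 6 months prior to the first dose of study medication" and exclusion 3 is "GFR < 30% of normal as measured within 6 months prior to the first dose of study medication".

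Section 3.3 requires progressive disease, shown by one of two routes. The first is a rate: "Skin thickness progression rate (STPR) ≥ 40, calculated as the mRSS at screening divided by time (in years) since the start of skin involvement". The second is recent change: "Worsening of mRSS within the last 6 months or shorter as judged by the physician together with the patient", with conditions on the number of skin sites. Inclusion 5 adds "Modified Rodnan Skin score (mRSS) ≥16 at baseline".

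The visit lists in Section 2.2 and the schedule in Appendix 1 contain no lung function test and no GFR measurement. Creatinine belongs to the chemistry panel at Visits 1 to 6 (Section 5.5.2.1), but no sentence says that GFR is derived from it or compared with exclusion 3.

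Exclusion 1 carries no date limit: "Ongoing Severe SSc manifestations, such as pulmonary arterial hypertension (PAH) with dyspnea NYHA III or more, scleroderma renal crisis". Exclusion 20 covers unstable disease only where it is unrelated to SSc.

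**The concern.** The look-back for the organ limits is about as long as the period over which patients are selected for change. A vital capacity or GFR result can satisfy the 6-month condition and still have been obtained before the worsening that made the patient eligible. If organ function has since fallen below the protocol's own limit, exclusions 2 and 3 as worded would not detect it, because the protocol generates no new value of either measure.

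Both limits are also written as exclusions. Read literally, a patient with no result in the window meets neither of them, and the protocol does not say that a result must exist.

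What is at stake is the entry check: a patient who is now beyond a limit that the sponsor chose could be dosed on an older and better value.

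**Working it through.** The protocol states no figure on this point, so there is none to reproduce. The check is one of dates.

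**Inputs**
- Minimum progression rate on the first route: 40 mRSS points per year, using the screening score (Section 3.3).
- Minimum skin score: 16 (Section 3.3). The protocol sets it at baseline; I assume that the screening score is the same.
- Screening to first dose: "After a screening period of 14 ± 7 days", so 7 to 21 days (Section 2.1).
- Look-back: 6 months before first dose (Section 3.4), taken as 365.25 / 2 = 182.6 days.

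**Rate route, mRSS 16**
1. Longest time since skin onset, at screening: 16 / 40 = 0.40 years = 146.1 days (4.8 months).
2. The rate uses the screening date but the look-back runs from first dose, so the screening interval is added: 146.1 + 7 = 153.1 days; 146.1 + 14 = 160.1 days; 146.1 + 21 = 167.1 days.
3. Part of the window before skin onset: 182.6 − 153.1 = 29.5 days; 182.6 − 160.1 = 22.5 days; 182.6 − 167.1 = 15.5 days. That is about 16 to 30 days at a rate of exactly 40, and more at a steeper rate.

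**Rate route, where the overlap ends.** At a rate of exactly 40, the score at which onset falls exactly 6 months before first dose is 40 × (182.6 − interval) / 365.25:

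| Screening interval | Overlap only below mRSS |
|---|---|
| 7 days | 19.2 |
| 14 days | 18.5 |
| 21 days | 17.7 |

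Higher scores need a steeper rate. At mRSS 30 the rate would have to exceed 30 / ((182.6 − interval) / 365.25), which is 62.4, 65.0 and 67.8 for the three intervals. At mRSS 30 and a rate of 40, onset can lie 30 / 40 = 0.75 years (9 months) before screening, so a 6-month-old value need not precede it.

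**Recent-worsening route.** No threshold applies. Whenever the worsening began after the test date, the value is older than the worsening. How often this happens cannot be calculated, because the protocol gives neither test dates nor dates of worsening.

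**Current safeguards, side by side**
- Kidney: exclusion 1 names renal crisis; creatinine is drawn at Visits 1 and 2; the investigator assesses laboratory results for clinical significance (Section 5.5.2.1). What is missing is the link from creatinine to the GFR limit.
- Lung: exclusion 1 names PAH with dyspnea, not reduced vital capacity; the Visit 1 physical examination includes the lungs (Section 5.5.2.2). No measurement is scheduled that could be set against the limit in exclusion 2.

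**The case against.** Several arguments on the other side are sound.

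- Six months is a maximum. Many values may be newer, and a value obtained after the worsening still does its job. A reader might infer that the limits fail the patients they were written for; that would need values to lie typically near the maximum age, and the protocol does not say so.
- A reader might also infer that an old value predates the disease. The rate is timed from the start of skin involvement, and nothing in the protocol equates skin onset with the onset of lung or kidney disease, or converts mRSS points into loss of vital capacity or GFR.
- It is tempting to put the cut-off at mRSS 20 (20 / 40 = 0.5 years). That leaves out the screening interval and overstates both the number of patients and the length of the overlap.
- Exclusion 1 has an open list and no date limit. Urine dipstick, blood pressure, ECG and an eligibility check are done at Visit 1 and again at Visit 2.
- Visit 1 lies inside the 6-month window, so exclusion 3 does not forbid using a GFR estimated from the screening creatinine. The protocol is silent rather than contrary.
- Contamination of the laboratory results is a weak argument. Section 6.1 summarizes laboratory values as ratios to day 0, so decline before entry sits in the baseline.

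These points limit the size of the concern but do not remove it. Exclusion 1 gives no lung-volume or GFR figure, exclusion 20 leaves out SSc-related decline, and the use of the screening creatinine for exclusion 3 is left to individual practice.

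**Conclusion.** The concern holds in a limited form. For some patients the vital capacity or GFR used at entry may be older than the qualifying skin worsening and may miss a later decline below the protocol's own limit. On the rate route, at exactly 40 and mRSS 16, about 16 to 30 days of the window precede skin onset, and at that rate the overlap exists only below mRSS 17.7 to 19.2. On the recent-worsening route it depends on dates that are not given.

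This rests on the 7 to 21 day screening interval, a 182.6-day look-back and equal skin scores at screening and baseline. The documents do not give the frequency of organ decline within 6 months, so the number of patients affected is unknown.

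The kidney is partly covered now, by exclusion 1 and by a creatinine result that is not tied to the limit. The gap is larger for the lung, where no test is scheduled. Neither the sample size nor the analysis is affected.

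**What to change.** **GFR.** Reconcile exclusion 3 with the Visit 1 chemistry. State that the existing GFR limit, unchanged, is also checked against GFR estimated from the Visit 1 creatinine. Name the estimating equation and the reference that defines normal, since the limit is a percentage of normal and the protocol gives neither. Weight and demography (taken here to include age and sex) are already recorded at Visit 1. No new sample is needed. The cost is one calculation per patient and possibly an occasional extra screen failure.

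**Vital capacity.** The sponsor should reconcile the 6-month look-back in exclusion 2 with inclusion 3 and say whether a value must exist for a patient to be eligible. No new time window or threshold is proposed here. A rule tied to the date of worsening would not work for patients who enter on the rate, who have no dated worsening, and it might require an additional test.

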## Removal of patients from therapy or assessment

Patients should stop study treatment for any of the following reasons:

- Increased disease activity requiring changes in SSc treatment
- Use of non-permitted concurrent therapy
- Pregnancy
- Non-compliance with the study drug (more than a total of 14 missed doses during the study) or study procedures.
- Lost to follow-up
- Occurrence of AEs that in the Investigators opinion, are not compatible with the continuation of patient participation in the study.

Patients are free to withdraw from the study at any time without providing reason (s) for withdrawal without prejudice to further treatment. Any patient can also be withdrawn from treatment on recommendation from the Investigator or the sponsor. The reason for withdrawal should be clearly described and documented in the CRF. For patients in the main study, an early withdrawal visit containing all procedures of the day 56 visit should, whenever possible and regardless of the reason for withdrawal, be performed, preferably on the day after the last dose of study medication or otherwise as soon as possible after the last dose of ABR-215757. In addition, a follow-up visit should be scheduled 4 weeks after the last dose of study medication.

Patients in the continuation phase who discontinue treatment should be called for a withdrawal visit containing the procedures of visit N[[2]](#footnote-3) as soon as possible after the last dose of ABR-215757. (see Appendix 1, Schedule of investigational events). A telephone follow-up should also be made 4 weeks after the last dose of study medication.

If a patient does not return for a scheduled visit, every effort should be made to contact the patient. In any circumstance, every effort should be made to document patient outcome.

Patients who are prematurely withdrawn from the study will not be replaced.

